## 6.7. SUBJECT COMPLETION AND WITHDRAWAL

### 6.7.1. Subject Completion

A subject will be considered to have completed the study if they complete all study procedures up to Visit IV inclusive, as described in the protocol.

### 6.7.2. Subject Withdrawal from Study

Subjects will be informed that they have the right to withdraw from the study at any time, without prejudice to their medical care, and that they are not obliged to state the reason(s). Any withdrawal must be fully documented in the End of Study page of the CRF and should be followed up by the Investigator.

The Investigator may withdraw a subject at any time if this is considered to be in the subject's best interest.

During the course of a study, the subject may be withdrawn for the following reasons:

- **Lack of efficacy:** Investigator judgment only. If subject's opinion only, check Subject Request. Explain in the eComment section of the eCRF End of Study page.
- **Adverse event:** Includes clinically significant new or worsening existing condition as judged by the investigator. Documented in the AE form.
- **Subject request:** Consent withdrawal, subject moved, schedule conflicts, etc. Specify the reason in the eComment section of the eCRF End of Study page.
- **Protocol violation:** Major protocol violation which would confound interpretation of the results. Specify the protocol violation in the eComment section of the CRF End of Study page.
- **Lost to follow-up:** Two documented phone calls and a registered letter requesting acknowledgement of receipt without response. Document in the eComment section of the CRF End of Study page.
- **Pregnancy:** **Study drug must be immediately discontinued.** Complete the Pregnancy Surveillance Form (see section 8.6 of protocol).
- **Missing return of menstruation:** Subjects having no return of menses for 6 months during a drug free period will be withdrawn.

- **Other:** Specify in the eComments section on the eCRF End of Study page. This reason should only be used if the reason for discontinuation is not better accounted for by another category.

Subjects who undergo any type of surgery or intervention which would interfere with study endpoints (i.e. hysterectomy, myomectomy, uterine artery embolization (UAE), etc.) will be discontinued from the study.

Subjects, who discontinue after at least four weeks of treatment with ulipristal acetate, will be asked to undergo the same assessments as those planned during visit IV, plus an endometrium biopsy.

Subjects, who discontinue prior to four weeks of treatment with ulipristal acetate, will be asked to attend a follow-up visit, which will include the same assessments as visit IV, without an endometrium biopsy.

Myoma size will not be measured if the subject has undergone uterine surgery.

### **6.7.3. Subject Replacement**

Subjects who discontinue the study will not be replaced.

## **6.8. PLANNED EXTENSION STUDIES**

No extension studies are planned.

# **7. INVESTIGATIONAL MEDICINAL PRODUCT AND OTHER DRUGS USED IN THE STUDY**

The term “Investigational Medicinal Product” (IMP) will refer to either the PregLem investigational drug undergoing study or any comparator drug, including placebo.

## **7.1. DESCRIPTION OF INVESTIGATIONAL MEDICINAL PRODUCTS**

PGL4001 (ulipristal acetate) is a steroid compound (17 $\alpha$ -Acetoxy-11 $\beta$ -(4-N,N-dimethylaminophenyl)-19-norpregna-4,9-diene-3,20-dione). PGL4001 10 mg is a 300 mg round, biconvex, white to off-white tablet containing 10 mg drug substance per tablet engraved with “ES10” on one side. Tablets are manufactured using direct compression process and are for oral administration. The tablets are packaged in blister pack (PVC/PE/PVDC-aluminium) and should be stored at ambient conditions and protected from light.

### **Study Drug: PGL4001**

INN: ulipristal (modified INN: ulipristal acetate)

|               |                                                                         |
|---------------|-------------------------------------------------------------------------|
| Active:       | PGL4001                                                                 |
| Form:         | Tablet                                                                  |
| Strength:     | 10mg                                                                    |
| Weight:       | 300mg                                                                   |
| Manufacturer: | Catalent Germany Schorndorf GmbH, and Gedeon Richter, Budapest, Hungary |

## 7.2. DOSAGE AND ADMINISTRATION

All subjects will be asked to take ulipristal acetate 10 mg tablet orally daily for 3 months (84 days) for each treatment course. There are four 3-month treatment courses in this study.

## 7.3. PACKAGING AND LABELLING

The packaging and label will be in accordance with applicable local regulatory requirements.

Ulipristal acetate 10mg tablets will be supplied by PregLem SA through Gedeon Richter (Budapest, Hungary) and Catalent Germany Schorndorf GmbH (Schorndorf, Germany) which will manufacture, pack, label, and ship them according to the current Good Manufacturing Practice (GMP) and European guidelines.

Responsibilities for manufacturing and packaging are provided in Table 1.

**Table 1: Responsibilities for Manufacturing and Packaging of PGL4001 tablets**

| Name and Address                                                                                                        | Responsibility concerning PGL4001 tablets                            |
|-------------------------------------------------------------------------------------------------------------------------|----------------------------------------------------------------------|
| Gedeon Richter Plc.
[name]
Hungary
[contact]
[contact]       | Manufacturing, primary packaging, quality control                    |
| Catalent Germany Schorndorf GmbH
[name]
[name]
Germany
[contact] | Labelling, secondary packaging, QP release, storage and distribution |

Quarterly study drug kits containing 12 blisters of 7 tablets each will be provided together with the corresponding release documents by the Sponsor PregLem S.A. via Catalent Germany Schorndorf GmbH.

As ulipristal acetate treatment is open-label, all subjects will receive boxes containing 12 blisters of 7 tablets of ulipristal acetate 10mg (quarterly kit).

Label examples are provided in the study file at the Investigator's site.

Each quarterly kit has one tear-off label containing the study number and the kit number. The subject will be given 2 quarterly kits for the first and second 3-month treatment courses at visit I and the other 2 quarterly kits for the third and fourth 3-month treatment courses at visit II. The tear-off labels will be taken from the boxes given to the subject and stuck on the subject log at each of these visits.

#### **7.4. PREPARATION, HANDLING AND STORAGE**

Ulipristal acetate tablets storage and shipment conditions are ambient and in blister pack (PVC/PE/PVDC)-aluminium. The blisters have to remain in the outer carton in order to be protected from light.

The storage facility at site should be locked and temperature-controlled.

The study drugs may be dispensed by the pharmacist or by a member of staff specifically authorised by the Investigator.

Any major deviations from the recommended ambient storage conditions should be immediately reported to the Sponsor, and the IMPs should not be used until authorisation has been given by the Sponsor.

#### **7.5. INVESTIGATIONAL MEDICINAL PRODUCT ACCOUNTABILITY**

The Investigator is responsible for ensuring investigational medicinal product accountability, including reconciliation of drugs and maintenance of drug records.

- Upon Receipt of IMP the Investigator (or pharmacist) will check for accurate delivery and acknowledge receipt by signing (or initialling) and dating the documentation provided by the Sponsor (or delegate) and returning it to the Sponsor (or delegate). A copy will be retained for the Investigator File.
- The dispensing of the IMP will be carefully recorded on the appropriate drug accountability forms provided by the Sponsor (or delegate) and an accurate accounting will be available for verification by the study monitor at each monitoring visit.
- IMP accountability records will include:
  - Confirmation of IMP delivery to the trial site in non-compromised conditions
  - The inventory at the site of IMP provided by the Sponsor
  - The use of each dose by each subject

- The return of full, partly used and empty blisters of IMP by each subject
  - The return to the Sponsor or alternative disposition of unused IMP.
  - Dates of IMP receipt, dispensation and returns, quantities, batch numbers, expiry dates and study numbers assigned to the subjects.
- The Investigator should maintain records that adequately document:
    - The subjects were provided with the doses specified by the protocol/amendment(s)
    - All IMP provided by the Sponsor were fully reconciled.

Unused IMP must not be discarded or used for any purpose other than the present study. IMP that has been dispensed to a subject must not be re-dispensed to a different subject.

The Study monitor will periodically collect the IMP accountability forms and check all investigational medicinal product dispensations and returns (both unused and used treatments) during the entire study period and prior to making arrangements for their return to the Sponsor (or delegate) in agreement with the Sponsor.

#### **7.5.1. Other drugs to be used in the study**

Not applicable.

#### **7.6. ASSIGNMENT TO TREATMENT GROUPS**

All subjects enrolled into the study will receive open-label treatment with ulipristal acetate. Each quarterly kit will bear a unique kit number to facilitate drug accountability. The blisters contained in the quarterly kit will bear the same kit number as the quarterly kit. Kit numbers will be 5 digits in length and will start with a leading V e.g. V0001, V0002, V0003 etc. The investigator will distribute 2 quarterly kits to the subject at visit I and the other 2 quarterly kits at visit II in a random order and, if applicable, dispense kits that will expire first.

#### **7.7. ASSESSMENT OF INVESTIGATIONAL MEDICINAL PRODUCT COMPLIANCE**

Subjects should be instructed to bring with them to each visit both opened and unopened Investigational Medicinal Product packages, in order to allow the assessment of compliance with study treatment. Investigational Medicinal Product administration must be recorded in the CRF (or the patient diary). The Study Clinical Research Associates (CRAs) will monitor subject's compliance during the entire study period.

#### **7.8. METHOD OF BLINDING**

Ulipristal acetate will be administered to all subjects in an open-label manner.

**7.9. EMERGENCY UNBLINDING**

Not applicable.

**7.10. TREATMENT OF OVERDOSE AND MISUSE**

An overdose is defined as any dose (i.e. quantity of drug given per administration or per day) above the maximum dosage defined in the protocol.

Misuse is the term used if more precise information is not available and additional information is needed to determine if there was a “medication error”, “drug abuse” or “overdose”.

Any details of overdose or misuse must be recorded in the study medication section of the eCRF.

Any case of overdose or misuse must be reported using an AE form or a SAE form, as applicable.

**8. ADVERSE EVENTS AND SERIOUS ADVERSE EVENTS**

Comprehensive assessments of any apparent toxicity experienced by the subject will be performed throughout the course of the study from the time of subject’s signature of informed consent. Study site personnel will report any adverse event, whether observed by the investigator or reported by the subject (see section 8.2.1, Eliciting Adverse Events).

The safety profile of ulipristal acetate will be assessed through the recording, reporting and analysis of baseline medical conditions, adverse events, physical examination findings including vital signs, gynaecological and breast examination, ovary and endometrium ultrasound, endometrium biopsies and laboratory tests.

The recording period for adverse events is described in section 8.5.

**8.1. ADVERSE EVENTS****8.1.1. Definitions****Adverse Event:**

An adverse event (AE) is defined as any untoward medical occurrence in a clinical trial subject administered an investigational medicinal product (IMP) and which does not necessarily have a causal relationship with this treatment. It can therefore be any unfavourable sign (including an abnormal laboratory finding), symptom, or disease temporally associated with the use of an IMP, whether or not considered related to the IMP.

For subjects for whom Visit F (in study PGL09-027) and Visit I of the current study are on different dates, events occurring prior to visit I and outside of study PGL09-027 are not to be reported as an adverse event in this study.

Events occurring after Visit I but prior to first IMP administration in the current study will be considered as adverse events due to previous administration of the IMP during previous study participation.

**Severity:**

The severity of AEs must be assessed by investigators according to the following definitions. The term “severity” is used to describe the intensity of a specific event. This has to be distinguished from the term “serious”.

|           |                                                                                                                                                 |
|-----------|-------------------------------------------------------------------------------------------------------------------------------------------------|
| Mild:     | The subject is aware of the event or symptom, but the event or symptom is easily tolerated (e.g. no reduction in daily activities is required). |
| Moderate: | The subject experiences sufficient discomfort to interfere with or reduce his or her usual level of activity.                                   |
| Severe:   | Significant impairment of functioning: the subject is unable to carry out usual activities and/or the subject’s life is at risk from the event. |

**Causality assessment:**

The causality assessment of an AE to the IMP will be rated as follows by the investigator:

|              |                                                                                                                                                                                         |
|--------------|-----------------------------------------------------------------------------------------------------------------------------------------------------------------------------------------|
| Not related: | There is no reasonable possibility of causal relationship between an AE and IMP.                                                                                                        |
| Related:     | There is at least a reasonable possibility of a causal relationship between an AE and an IMP. This means that there are facts (evidence) or arguments to suggest a causal relationship. |

**8.1.2. Abnormal laboratory findings and other objective measurements**

Abnormal laboratory findings and other objective measurements (e.g. blood pressure, endometrium biopsy, ultrasound measurements) must be reported as an Adverse Event only if assessed by the investigator as “clinically significant” e.g. meeting at least one of the following conditions:

1. The abnormality suggests a disease and/or organ toxicity AND this abnormality was not present at the baseline (visit F in PGL09-027) or is assessed as having evolved since the baseline visit.
2. The abnormality is a Serious Adverse Event
3. The abnormality results in discontinuation of the IMP
4. The abnormality requires medical intervention or concomitant therapy

The investigator must initial and date each laboratory report/CRF page and note directly on the report/CRF page whether or not each out-of-range laboratory result is clinically significant. The outcome of this assessment will be reported using an AE or SAE form, as appropriate.

When reporting an abnormal laboratory finding in the AE page of the eCRF, a clinical diagnosis should be recorded rather than the abnormal value itself, if available (for example, “anaemia” rather than “decreased red blood cell count”)

For all of these adverse events, whether or not related to the treatment, the laboratory test(s) will be followed-up as appropriate.

### **8.1.3. Baseline Medical Conditions**

Medical conditions present at the baseline visit (visit I in the current study PGL11-024) that do not worsen in severity or frequency during the study (PGL11-024) are defined as Baseline Medical Conditions. These medical conditions should be adequately documented on the “medical history page of the eCRF”. Baseline Medical Conditions, excluding the disease under study (refer to 8.1.4), that worsen in severity or frequency during the study should be recorded and reported as adverse events.

### **8.1.4. Exacerbation of uterine myoma**

In this protocol, symptoms and signs of exacerbation or worsening of uterine myoma will usually be captured in the context of efficacy assessment, and recorded in the relevant sections of the eCRF. Therefore, symptoms, exacerbation or worsening of uterine myoma will NOT be considered as adverse events nor captured on the AE page of the eCRF unless clinically significant and not consistent with the anticipated natural progression of the disease.

Lack of efficacy of the IMP is NOT considered as an adverse event.

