### 1.2. UTERINE MYOMA

Uterine myomas are benign, monoclonal, hormone-sensitive, smooth muscle tumours of the uterus. They are the most common tumour of the female reproductive tract in pre-menopausal women and

mostly asymptomatic affecting approximately 40% of women between 35 and 55 years. When symptomatic, the main symptoms are heavy uterine bleeding, abdominal pressure, abdominal pain, increased urinary frequency and infertility. Anaemia may occur as a consequence of heavy bleeding. Besides causing physical morbidity, uterine myomas are a frequent cause of significant impairment of Quality of Life (QoL) . They are also a leading cause of hysterectomy .

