### **8.1.5. Adverse Events of Special Interest**

An Adverse Event of Special Interest (AESI) is an adverse event of scientific or medical concern specific to the Sponsor or the particular product or program, for which ongoing monitoring and rapid communication by the investigator to the Sponsor may be appropriate. It may require further investigation in order to characterise and understand them. It could be serious or non-serious, and could include events that might be potential precursors or prodromes for more serious medical conditions in susceptible individuals.

The AEs of special interest for this protocol have been pre-defined as follows:

- Any intervention for endometrium thickening, which is undertaken outside the protocol (surgical intervention, endometrial biopsy or medical treatment).
- Any diagnosis of endometrium biopsy other than benign endometrium done by local pathologists (biopsy performed outside the protocol).
- Acute uterine bleeding requiring immediate intervention (dilatation, curettage, other surgery or blood transfusion).
- Drug Induced Liver Injury (DILI questionnaire to be filled also).

Any AESI should be reported to Sponsor as described in section 8.3.3.

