### 8.3.3. Study specific reporting procedure

With any **AE of Special Interest (AESI)** occurring during this trial (see section 8.1.5), regardless of causal relationship and expectedness, the Investigator is to follow the reporting procedure as follows:

- Take prompt and appropriate medical action, if necessary, the safety of study subjects is the first priority.
- Complete the AE form in the eCRF. Complete as appropriate the AESI form or SAE form (and DILI form, if applicable), E-mail (or fax) the completed and signed form(s), accompanied by the CRF pages of demographic, medical history, previous treatments, non-drug therapy and concomitant treatments pages of the eCRF, and laboratory results (as appropriate) immediately to **UBC Safety Europe, (contact numbers in section 8.3.2), but not later than 24 hours.**
- Monitor and record the progress of the event until it resolves or reaches a clinically stable outcome, with or without sequelae. All additional follow-up evaluations must be reported by the site to **UBC Safety Europe** as soon as possible but **not later than 24 hours after notice**. AESIs will be followed until the Investigator and Sponsor agree that the event is satisfactorily resolved.
- Obtain and maintain sufficient source documentation of pertinent medical records, relevant information, and medical judgments from colleagues who assisted in the treatment and follow-up of the subject. If necessary, contact the subject's personal physician or hospital staff to obtain further details.

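### Section 8.1.4 keeps myoma worsening off the AE page with no exception for the acute uterine bleeding that 8.1.5 and 8.3.3 require to be recorded as an AESI, and the text does not say which rule prevails

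*Protocol*

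**What the plan says.** Three parts of protocol section 8 bear on the same kind of event.

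- **Section 8.1.4 (exacerbation of uterine myoma)** starts from the premise that worsening "will usually be captured in the context of efficacy assessment". It concludes that these symptoms "will NOT be considered as adverse events nor captured on the AE page of the eCRF unless clinically significant and not consistent with the anticipated" course of the disease, which the section calls natural progression. Both conditions must be met before the event is recorded. The section adds that lack of efficacy is not an adverse event.
- **Section 8.1.5 (AESIs)** opens with: "An Adverse Event of Special Interest (AESI) is an adverse event of scientific or medical concern". The third of its four pre-defined items is "Acute uterine bleeding requiring immediate intervention (dilatation, curettage, other surgery or blood transfusion"). No condition on natural progression is attached, and any AESI is sent to section 8.3.3.
- **Section 8.3.3 (study-specific reporting)** covers any AESI: "regardless of causal relationship and expectedness, the Investigator is to follow the reporting procedure as follows". One of its steps is "Complete the AE form in the eCRF", with the forms sent to the safety unit within 24 hours.

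Section 1.2 describes symptomatic myoma and says "the main symptoms are heavy uterine bleeding, abdominal pressure, abdominal pain", among others.

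**The concern.** Heavy bleeding is both a leading symptom of the disease under study and, when acute and needing immediate intervention, a pre-defined AESI. An investigator who judges such a bleed to be part of the expected course of myoma finds that it fails the second condition of 8.1.4. On that section's wording it does not go on the AE page. Sections 8.1.5 and 8.3.3 say that it does. Neither 8.1.4 nor 8.1.5 refers to the other, and no sentence ranks them.

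The conflict concerns what is collected, not how it is analysed. An event that was never entered cannot be tabulated later, so an analysis plan cannot repair it. Long-term safety is a stated objective (section 2.2), and the number and proportion of women with treatment-emergent AEs is a safety endpoint (section 3.2). Omitting a bleed can only lower the AE and AESI counts. It would also remove that event from the 24-hour AESI notifications.

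**Working it through.** The point rests on comparing the rules; the protocol gives no figure to reproduce.

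**Step 1: the rules side by side, for an acute bleed attributed to myoma and needing immediate intervention.**

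| Question | 8.1.4 | 8.1.5 with 8.3.3 |
|---|---|---|
| Is it an adverse event? | Only if clinically significant and also inconsistent with natural progression | Yes; an AESI is defined as an adverse event |
| Is natural progression tested? | Yes | No |
| Is it on the AE page? | No, if judged consistent with natural progression | Yes |
| Is it notified within 24 hours? | Not addressed | Yes |

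The rules give opposite answers only for bleeds that the investigator judges consistent with natural progression. The 8.1.5 item is not restricted to bleeding caused by myoma, so the overlap is partial.

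**Step 2: does 8.3.3 override the 8.1.4 test?** Its scope clause sets aside causal relationship and expectedness. The 8.1.4 test is neither of these: it asks whether the event fits the anticipated course of the disease. The clause therefore does not remove that test in terms. Because 8.1.5 defines an AESI as an adverse event, a reader who uses 8.1.4 to decide what counts as one may never reach 8.3.3.

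**Step 3: would the efficacy data catch the bleed instead?** This is the premise of 8.1.4.

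- The bleeding chart covers 8 days of one menstruation, at the re-start of the first course (section 6.3.4).
- The satisfaction, quality-of-life and pain questionnaires are completed at visits and do not log an acute bleed as an event.
- The exploratory endpoint on surgery or invasive procedures (section 3.3) would not register a bleed managed by transfusion alone.

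**Step 4: a contrast within section 8.** Under 8.1.2, an abnormal finding is reportable if it meets at least one of several conditions, including being a serious adverse event or requiring medical intervention. Section 8.1.4 has no such safeguard.

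**Step 5: scale.** Section 9.2 anticipates about 70 to 90 subjects. One omitted woman with no other treatment-emergent AE changes the AE proportion by 1/N:

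- N = 90: 1/90 = 0.011, or 1.1 percentage points.
- N = 70: 1/70 = 0.014, or 1.4 percentage points.

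The documents give no expected frequency of such bleeds, so the number of women affected cannot be computed.

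**The case against.** The best counter-argument is that the specific rule governs. Section 8.1.5 names this event, attaches no natural-progression condition and sends it to a reporting procedure that demands the AE form. Section 8.1.4 is a general statement about myoma symptoms, resting on what usually happens. Every woman in the trial has myoma, so letting 8.1.4 override would largely empty the bleeding item in 8.1.5. This stands as the likely intent and the ordinary reading. It does not settle the matter: the hedge in 8.1.4 qualifies only where worsening is usually captured, the operative exclusion is unhedged, and 8.1.4 can itself be read as the specific rule because it addresses the disease under study.

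A second argument is that serious bleeds have another route. Sections 8.3.1 and 8.3.2 require an SAE report for any untoward occurrence meeting a seriousness criterion, whatever its relationship or expectedness. The exemptions for disease management and scheduled surgery sit under the hospitalisation criterion only. Many bleeds needing urgent surgery or transfusion could qualify as life-threatening or medically important. Surgery that interferes with the endpoints also leads to documented discontinuation (section 6.7.2). This narrows the gap considerably, but a bleed treated by transfusion alone and judged non-serious would still escape.

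A reader might also infer from section 1.2 that investigators will usually regard such bleeds as natural progression. The documents do not support that. Section 1.2 lists heavy bleeding as a symptom and mentions anaemia; it does not describe acute bleeding that needs immediate intervention as the anticipated course. Section 1.1 says drugs of this class induce amenorrhoea in the majority of women. Such a judgement is possible, but its frequency is unknown.

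**Conclusion.** The conflict is real but limited. Two recording rules in the protocol can give opposite answers for a myoma-related acute bleed needing immediate intervention, and nothing says which prevails. The AESI rule is the likely intent. A site that applies 8.1.4 first can nonetheless omit the event from the AE and AESI data, and the efficacy assessments would not reliably record it. The effect runs one way, towards a lower safety count.

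Two stronger readings are tempting and should not be drawn. One is that these events are in fact counted at some sites and not at others, so that the reported rate reflects site interpretation. The text creates room for that but neither prescribes nor shows it. The other is a numerical estimate of the loss. For example, an assumed rate of 2 to 5% among 80 women would give 0.02 × 80 = 1.6 to 0.05 × 80 = 4 women, but nothing in the documents anchors that rate, and losing all of them would require every investigator to set the named AESI aside. The supportable figure is 1.1 to 1.4 percentage points per omitted woman, assuming 90 to 70 treated subjects and no other AE in that woman.

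**What to change.** Reconcile the passages with one sentence in section 8.1.4, for example: *This exclusion does not apply to events listed in section 8.1.5 or to events meeting a seriousness criterion in section 8.3.1; these are always recorded on the AE page, whether or not they fit the natural course of the disease.* The first half resolves the conflict; the second keeps the AE page consistent with the SAE reporting in 8.3.1 and 8.3.2. A cross-reference from 8.1.5 back to 8.1.4 would help sites. The AE and AESI tables should follow the same rule.

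The change affects recording only and leaves clinical management untouched. It costs a sentence and a note to sites. The downside is a slightly less favourable AE and AESI count, because some bleeds that might have been left off would be included.
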